### Study Population

#### Inclusion Criteria

Preterm infants receiving care within the Neonatal Intensive Care Unit at CCDHB or healthy term infants at 39–40 weeks’ gestation from low-risk pregnancies delivered at CCDHB.

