### Sample Size

This study will be the first observational study of creatine homeostasis in the preterm infant that encompasses plasma, urine, nutrition, and cerebral creatine measures across time. As the outcomes are mainly descriptive, no formal power calculation has been performed. However, ^1^H-MRS results reported by Koob et al. (2016) showed comparison of 13 preterm vs term infants allowed for measurement of a statistically significant (−17%) reduction in cerebral creatine content in preterm infants at CPA (tCr/H_2_0 × 10^−3^; term 0.12 ± 0.1 vs preterm 0.10 ± 0.1). This same study had a 20–25% failure rate in obtaining accurate MRI/^1^H-MRS measurements at CPA (Koob et al., 2016). Taking these data into consideration and a potential loss to follow-up at 3-month of 20%, we aim to capture 20 infants in each gestational group.

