### Statistical Analysis

Characteristics of the population will be tabulated, along with appropriate descriptive statistics of the study sample. Continuous data will be assessed for normality and expressed as means and standard deviations or median and interquartile range as appropriate. Categorical data will be expressed as counts and proportions. Average creatine content from nutrition per week for each baby in the early postnatal period will be calculated.

Differences in creatine and GAA measures (^1^H-MRS, plasma or urine) between infants born preterm and those born at term will be assessed at CPA using a t-test or Mann-Whitney U test as appropriate. The correlation between gestational age at birth and creatine and GAA measures at CPA will also be determined using a Spearman or Pearson correlation. Preterm infant plasma and urine creatine and GAA concentrations and creatine:GAA ratio in the early postnatal period will be described and plotted. Associations between cerebral creatine content, plasma and urine creatine concentrations with maternal, and infant characteristics at CPA will be determined using Spearman or Pearson correlations for continuous data (maternal age, gestational age, birth weight, parity, gravity, placental weight) or a t-test or Mann-Whitney U test for categorical data (infant sex, mode of delivery, maternal comorbidities, country of birth, ethnicity, and dietary preferences), as appropriate. Differences in creatine, GAA, and amino acid content of nutrition sources (TNP, formula or breast milk) will be determined using a one-way ANOVA or Kruskal-Wallis H test as appropriate. The association between creatine, GAA, and amino acid content of nutrition sources (TNP, formula or breast milk) and infant plasma and urine creatine at CPA will be assessed using a Spearman or Pearson correlation as appropriate. Finally, the association between cerebral creatine content, plasma creatine levels, and the ratio of plasma:cerebral creatine at CPA with GMA, MRI global injury, and DAYC-2 scores will be determined using linear regression at both CPA and at 3 months’ corrected postnatal age. Potential confounders such as gestational age and maternal and infant characteristics will be assessed, along with collinearity, prior to performing multivariable linear regression.

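### Aim 3 analysis: two-group tests are named for a three-level variable, and birth weight, placental weight, comorbidity and probably mode of delivery are tested without gestational age, to which the design ties them

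*Protocol article*

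**What the plan says.** The third item under Specific Aims is to describe how cerebral, plasma and urine creatine relate to maternal and infant characteristics at term corrected age. The Statistical Analysis section carries this out one variable at a time. It uses "Spearman or Pearson correlations for continuous data (maternal age, gestational age, birth weight, parity, gravity, placental weight") and, for the categorical characteristics, a "t-test or Mann-Whitney U test for categorical data (infant sex, mode of delivery, maternal comorbidities, country of birth, ethnicity, and dietary preferences"). Gestational age is one entry in the first list; it is not an adjuster for the others.

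Four other places bear on this:

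- **Monitoring and Data Collection** records diet as omnivorous, vegetarian or vegan, which is three levels. It names four maternal conditions: preeclampsia, gestational diabetes, chorioamnionitis and IVF.
- **Statistical Analysis**, on the content of the three nutrition sources, says that differences "will be determined using a one-way ANOVA or Kruskal-Wallis H test as appropriate".
- **Recruitment** and **Sample Size** set five gestational strata from 23 to 40 weeks ("we aim to capture 20 infants in each gestational group"), with equal numbers of each sex. **Inclusion Criteria** require term infants to be healthy and "from low-risk pregnancies delivered at CCDHB". **Exclusion Criteria** remove infants with birth weight below the 10th customised percentile.
- **Statistical Analysis** ends with: "Potential confounders such as gestational age and maternal and infant characteristics will be assessed, along with collinearity, prior to performing multivariable linear regression". The sentence just before it concerns associations of creatine "with GMA, MRI global injury, and DAYC-2 scores will be determined using linear regression at both CPA and at 3 months".

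**The concern.** **Test choice.** A t-test or Mann-Whitney U test compares two groups. With three diet levels the analyst must either merge levels or test pairs, and the article says neither. An unplanned merge leaves a choice open after the data are seen, and pairwise testing raises the error rate. The same section handles another three-level factor correctly, so the text is inconsistent with itself.

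**Confounding built into the design.** The study hypothesises that creatine at term corrected age depends on prematurity. Birth weight and placental weight rise with gestation, and excluding growth-restricted infants ties birth weight to gestation more closely still. Selecting low-risk term pregnancies concentrates comorbidity among preterm infants. An unadjusted test of any of these against creatine will therefore partly pick up gestational age. At stake is the reading of Aim 3: an association that only reflects prematurity could be reported as if it belonged to the characteristic. The Discussion says the data will supply effect sizes for later studies, so confounded estimates could be carried forward.

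**Working it through.** **Inputs from the article.** Five groups of 20, so 80 preterm and 20 term infants; mean cerebral creatine 0.12 (term) and 0.10 (preterm); SD printed as 0.1; three diet levels. No alpha is stated, so two-sided 5% is assumed. Also assumed: SDs of 0.03, 0.02 and 0.01; comorbidity in 40% of preterm and 0% of term infants; one of two modes of delivery in 55% of preterm and 25% of term infants; level counts above three.

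**Why smaller SDs are shown.** The printed difference is (0.10 − 0.12)/0.12 = −16.7%, which agrees with the stated −17%. With 13 infants per group (an assumed reading) and SD 0.1, t = 0.02/(0.1 × √(2/13)) = 0.51, p = 0.61. That does not give the significance the article reports. SD 0.02 gives t = 2.55, p = 0.018; SD 0.01 gives t = 5.1. The printed SD is therefore doubtful, and results are given with it and with smaller values.

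**Step 1: two-group tests on several levels.** Three independent tests would give 1 − 0.95³ = 14.3%. Simulated with no true effect, 100 infants:

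| Levels | Any pairwise t-test p < 0.05 | One-way ANOVA |
|---|---|---|
| 3 | 12% | 5% |
| 4 | 20% | 4% |
| 5 | 28% | 5% |

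Splitting the three diet levels unequally (85, 10 and 5 infants) also gives 12% against 5%.

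**Step 2: spurious comorbidity difference.** Suppose comorbidity has no effect of its own and occurs only in preterm infants, with prevalence p. The comorbid group then has mean 0.10. The other group mixes 20 term infants with 80(1 − p) preterm infants, so it is higher by 0.02 × 20/(20 + 80(1 − p)):

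- p = 20%: 0.40/84 = 0.0048
- p = 40%: 0.40/68 = 0.0059
- p = 60%: 0.40/52 = 0.0077

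That is 4.0%, 4.9% and 6.4% of the term mean. The SD affects only how often the difference is detected.

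**Step 3: false-positive rates.** In 2,000 simulated trials per setting, creatine depends only on gestational age, either as a preterm-term step or as a linear trend, and no characteristic has its own effect. Birth weight is modelled as falling about 10% for each week before 40, with log-scale SD 0.12 (assumption). Unadjusted rates at nominal 5%, with ranges covering both shapes:

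| Characteristic | SD 0.1 | SD 0.03 | SD 0.02 | SD 0.01 |
|---|---|---|---|---|
| Birth weight | 10-17% | 59-90% | 91-100% | 100% |
| Any comorbidity | 5% | 14% | 21% | 47-60% |
| Mode of delivery | 5% | 9-11% | 13-15% | 27-33% |
| Infant sex (balanced) | 5-6% | 3% | 3-4% | 0.5-1.5% |
| Maternal age (assumed unrelated to gestation) | 5% | 5% | 4-6% | 5% |

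With 16 evaluable infants per group and SD 0.02, the rates are 83-100% for birth weight, 18% for comorbidity and 11-13% for mode of delivery.

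**Step 4: after adjustment.** With gestational age and term status in a linear model, every rate above returns to 4-6%. A linear gestational-age term alone may not be enough: under the step shape at SD 0.01, mode of delivery still gave 11%.

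Placental weight was not simulated; the argument is the same as for birth weight. Only cerebral creatine was simulated, because the article gives no plasma or urine figures.

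**The case against.** The strongest reply is that Aim 3 only sets out to describe associations, and the article calls its outcomes mostly descriptive. If creatine is lower after preeclampsia because those infants were born early, the unadjusted association is real. It is a false positive only for an effect independent of gestation. Gestational age may also lie on the path from comorbidity to creatine, so adjusting changes the question. This stands as a reason to keep the unadjusted description. It does not remove the need for an adjusted analysis beside it, since the plan uses hypothesis tests and means to pass on effect sizes.

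A second reply is that the closing confounder sentence names no outcome and could cover Aim 3. That reading is possible. But the sentence follows directly on the neurodevelopment regressions, and no regression of creatine on characteristics is named anywhere.

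A third is that coding is commonly left to a fuller document. This has force for ethnicity and country of birth, whose levels are not given, and for comorbidities, each of which can be coded yes or no and then suits a t-test. It does not help diet, whose three levels the article itself states.

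A reader might go further and infer three things that the article does not support:

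- That the characteristics as a whole mostly restate the preterm-term contrast. Sex is balanced by design, and nothing ties maternal age, parity, gravity, ethnicity, country of birth or diet to gestation.
- That the two-group tests cause the confounding. The two faults are independent.
- That Aim 3 results would misdirect the choice of infants for the later trial. The Discussion describes supplementation after premature birth if the overall hypothesis is supported; it does not say these correlates would select infants.

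**Conclusion.** The point holds in two limited parts.

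1. The named tests are wrong as written for dietary preference, and probably for ethnicity and country of birth. If the gap were filled by pairwise testing, the chance of a false positive would be about 12% for three levels instead of 5%.
2. The associations of creatine with birth weight, placental weight, maternal comorbidities and plausibly mode of delivery are confounded with gestational age by design, and the article specifies only unadjusted tests for them.

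The size of the second part is uncertain. Under the assumed prevalences, the spurious comorbidity difference is 4-6% of the term mean. Its false-positive rate is close to nominal at the printed SD of 0.1 and clearly raised at SDs of 0.03 to 0.01. Birth weight is raised at every SD examined. These figures rest on assumed SDs, prevalences and a birth-weight model, and on creatine depending on gestational age alone. Infant sex is not affected, and for the other characteristics confounding is not shown.

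**What to change.** 1. For dietary preference, and for ethnicity and country of birth if they have more than two levels, name one-way ANOVA or Kruskal-Wallis, as the section already does for nutrition source. Alternatively, fix a merge to two levels before the data are seen, for example omnivorous versus not.
2. For birth weight, placental weight, maternal comorbidities and mode of delivery, keep the unadjusted description. Add a linear model of each creatine measure on the characteristic plus gestational age at birth and an indicator for the term group, or analyse the preterm infants alone with gestational age in the model.
3. Estimate comorbidity effects within the preterm infants, since a low-risk term group offers little or no comparison.
4. State whether the closing confounder sentence applies to Aim 3 as well as to the neurodevelopment regressions.

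No new data are needed; all these variables are already collected. The cost is slightly more analysis, some loss of precision and fewer nominally significant correlates.

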### Primary Outcome Measures

Cerebral creatine content at term CPAPlasma (bi-weekly) and urine (weekly) creatine and GAA levels from birth until hospital discharge and at CPACreatine, GAA, and amino acid levels in infant nutrition (TPN, formula, or breast milk) supplied from birth until discharge and at CPA

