### Sample and Data Collection

#### Blood, Urine, and Nutrition Sampling

A schematic overview of the sampling regime for each participant is outlined in Figure 1. At the time of birth, we will use a finger prick to collect ~120 μl of maternal whole blood using a capillary tube. A 2-ml venous cord blood sample will also be collected from which a ~120 μl sample will be obtained using a capillary tube. Then, while infants are receiving care in the NICU, or on postnatal wards, and at follow-up appointments, the following samples will be collected. Sample frequency will be dictated by gestational age at birth.

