**Figure 1 fig1:**
[figure not shown]
Schematic representation of UNICORN sampling regime. Samples of neonatal blood, urine, and nutrition will be collected weekly or bi-weekly for the duration of the infants stay in hospital. Magnetic resonance imaging (MRI) and magnetic resonance spectroscopy (^1^H-MRS) will be performed at term corrected postnatal age (CPA). Infants will also undergo a general movements assessment (GMA) at CPA and at 3 months CPA. At the follow-up appointment at 3 months CPA, further neurological assessment will be completed using the Developmental Assessment of Young Children – Second Edition (DAYC-2) assessment tool.

**Blood sampling**: A blood sample will be collected biweekly. We will perform a heel prick to collect ~120 μl of whole blood using a capillary tube. All blood samples (cord, maternal, or infant) will be transferred to a Hemaspot™ SE blood separation device to facilitate collection of the cell-free blood fraction (referred to throughout as plasma for clarity) from a small volume of whole blood. Hemaspots are allowed to dry at room temperature before being stored at −20°C for future analysis.

**Urine sampling**: Around the same time as the blood collection, and on each alternate week, we will place some gauze into the infant’s nappy to facilitate a spot urine collection. Once obtained, this sample will be transferred to an Eppendorf tube and stored at −80°C for future analysis.

**Nutrition sampling**: A 200 μl sample of the nutrition (TNP, formula, and breast milk) being fed to each infant at the time of the blood and urine sampling will be collected. If in powdered form (formula), this will be reconstituted following standard practices. All samples will be transferred into an Eppendorf tube and stored at −80°C for future analysis.

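### The test comparing creatine, GAA and amino acid content between TPN, formula and breast milk assumes independent observations, but the feed samples are serial and the plan names no unit of analysis.

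*Protocol article*

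**What the plan says.** The third primary outcome is the creatine, GAA and "amino acid levels in infant nutrition (TPN, formula, or breast milk) supplied from birth until discharge and at CPA" (Primary Outcome Measures). Comparing these concentrations between feeds is also one of the Specific Aims.

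The samples are serial by design. The legend to Figure 1 says: "Samples of neonatal blood, urine, and nutrition will be collected weekly or bi-weekly for the duration of the infants stay in hospital". The nutrition sampling paragraph adds that a sample of whatever is "being fed to each infant at the time of the blood and urine sampling will be collected". The number per infant is not fixed: "Sample frequency will be dictated by gestational age at birth" (Blood, Urine, and Nutrition Sampling).

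For the comparison between feeds, the Statistical Analysis section says that differences in the "content of nutrition sources (TNP, formula or breast milk) will be determined using a one-way ANOVA or Kruskal-Wallis H test". It names no term for mother, infant, product or batch, and does not say what counts as one observation. The only averaging step in that section is: "Average creatine content from nutrition per week for each baby in the early postnatal period will be calculated". Continuous data are to be "expressed as means and standard deviations or median and interquartile range as appropriate". On sample size the article says: "As the outcomes are mainly descriptive, no formal power calculation has been performed".

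**The concern.** One-way ANOVA and Kruskal-Wallis both treat every value as an independent draw from its source. Choosing between them on normality does nothing about dependence.

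The sampling scheme produces dependence in three ways. Successive breast milk samples from one mother resemble each other. Formula and TPN samples probably come from products shared by several infants, so a further draw adds little new information about that type of feed. An infant may also move from one source to another during the stay, so the three groups need not be separate sets of infants.

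The weekly average does not remove the problem. It covers creatine only, it is not tied to this test, and it leaves several weeks per infant and shared products across infants.

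At stake is a false finding that feeds differ in creatine or precursor content. The Discussion says the study would inform a randomised trial of dietary creatine supplementation, so this comparison could carry weight beyond description.

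**Working it through.** **The plan's own figure.** The article gives no figure for the nutrition comparison. Its 20 infants per gestational group rests on cerebral creatine: 13 infants, with 20–25% failed scans and 20% lost, gives 13/0.80/0.80 = 20.3 to 13/0.75/0.80 = 21.7, close to 20. This has no bearing on the feed comparison.

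**Inputs.** From the article: three sources, serial sampling, a one-way test. Assumed, because the article does not give them: two-sided alpha 0.05, 20 mothers or products (clusters) per source, m = 2, 4 or 8 samples per cluster, and an intraclass correlation (ICC) of 0.1, 0.3 or 0.5.

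**Formula.** The design effect is D = 1 + (m − 1) × ICC. With three sources the numerator has 2 degrees of freedom, so when all samples are pooled the large-sample type I error is about 0.05^(1/D).
- m = 2, ICC 0.1: D = 1.1; 0.05^(1/1.1) = 6.6%.
- m = 4, ICC 0.3: D = 1.9; 0.05^(1/1.9) = 20.7%.
- m = 8, ICC 0.5: D = 4.5; 0.05^(1/4.5) = 51.4%.

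**Simulation.** Normal data, no true difference between sources, every sample entered separately, 3,000 runs per cell. Type I error of ANOVA, with Kruskal-Wallis in brackets:

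| Samples per cluster | ICC 0 | ICC 0.1 | ICC 0.3 | ICC 0.5 |
|---|---|---|---|---|
| 2 | 4.9% (4.4%) | 6.0% (5.8%) | 9.1% (9.0%) | 14.3% (13.6%) |
| 4 | 4.9% (4.6%) | 10.6% (9.9%) | 21.7% (19.9%) | 32.9% (31.4%) |
| 8 | 5.3% (5.2%) | 17.2% (16.4%) | 38.0% (36.9%) | 51.9% (51.3%) |

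The formula and the simulation agree to within about 3 percentage points. The rank test offers no protection.

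**One mean per cluster.** With the same data collapsed to one mean per mother or product, the simulated error was about 4–7% throughout. For ANOVA on balanced normal data it is 5% in theory, so that spread is simulation noise.

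**A few products.** Suppose 40 mothers with 4 samples each, 3 formula products with 40 samples each and 3 TPN products with 40 samples each. Pooled ANOVA then gives 45%, 71% and 82% at ICC 0.1, 0.3 and 0.5. Collapsing to means gives 0.3%, 1.5% and 3.1%. That is conservative, because the product means average 40 samples and the mothers' means only 4, and with three products per group the test says little.

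**The case against.** The strongest reply is that the article never says the serial samples are pooled. A reader might infer from the named test that the plan does treat them as independent and that its p-values are therefore wrong. The text does not support that as a fact: the unit of analysis is unstated, and the same test on one mean per mother or product would largely hold its error rate. A journal article may also leave such detail to a fuller document. This stands as a limit, so the inflation is conditional. It does not dispose of the point. The article fixes a test that does not fit the samples as collected, and the one averaging step it names would not make it fit.

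A reader might also infer that the planned summaries or error bars are wrong. They are not shown to be: only SD or IQR is planned, with no standard errors or confidence intervals. Clustering barely moves a pooled SD. With 20 clusters of 6 and ICC 0.7, D = 1 + 5 × 0.7 = 4.5, and the expected sample variance is (120 − 4.5)/119 = 0.97 of the true value, so the SD is about 1.5% too low.

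That formula and TPN come from only a few products is likewise an inference. The article does not give the number, or say whether TPN is standardised.

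Finally, the study is observational and mainly descriptive, and its central hypothesis concerns creatine in infants, not in feeds. That lowers the severity. It does not excuse a hypothesis test on a listed primary outcome whose assumption the sampling does not meet.

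**Conclusion.** The point holds in conditional form. The stated test needs independent observations, the sampling gives repeated ones, and nothing in the article reconciles the two. If each serial sample counts as an observation, the nominal 5% error becomes about 6% in the mildest case examined (2 samples, ICC 0.1) and about 52% in the most severe (8 samples, ICC 0.5), with 20 clusters per source. It would be higher still if a few products supplied many samples. If the analysis uses one value per mother or product, most of the problem goes away.

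The size rests on assumed ICCs, samples per cluster and numbers of mothers and products. The direction does not: any positive within-cluster correlation makes the pooled p-values too small. This should be fixed. It does not affect the planned descriptive summaries and does not undermine the study as a whole.

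**What to change.** State the unit of analysis: the mother for breast milk, the product or batch for formula and TPN. Then do one of the following:

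- Collapse to one mean per mother or product before the stated test. This is the simplest route and keeps the named tests.
- Fit a linear mixed model with source as a fixed effect and random intercepts for mother or product/batch.

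If there turn out to be only a few formula or TPN products, describe those feeds by product and do not test them. A product variance component would be poorly estimated, and a test on three means per group is uninformative.

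Record the formula product and TPN batch at each sampling, because these may be hard to recover later. Report the number of mothers and products per source beside the number of samples.

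The cost is a sentence or two in the analysis section and two extra data fields. The comparison will have fewer effective observations and larger p-values, which reflects the information actually collected.

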### Specific Aims

Compare cerebral, plasma, and urine creatine and GAA content between preterm and term infants at CPA.Describe preterm infant plasma and urine creatine and GAA concentrations and creatine:GAA ratio in the early postnatal period.Describe associations between cerebral creatine content, plasma, and urine creatine concentrations with maternal and infant characteristics at CPA.Compare creatine, GAA, arginine, glycine, and methionine concentrations in standard preterm nutrition, including TPN, preterm infant formulas, and breast milk.Determine whether dietary source of creatine (TPN, formula, or breast milk) is related to plasma or urine creatine concentrations in the early postnatal period.Describe associations between cerebral creatine content and blood and urine creatine concentrations with neurological outcomes (GMA, MRI, and DAYC-2) at CPA and at 3 months of corrected postnatal age.

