#### MRI/^1^H-MRS Data Acquisition

At 40 weeks of corrected postnatal age (CPA), each participant will undergo a MRI/^1^H-MRS scan. MR examinations will be performed on a Siemens 3T Skyra using a 16-channel dedicated pediatric head coil. Infants will be examined without sedation using a “feed and wrap” technique according to standard institutional practice. In brief, infants are brought to the MRI unit, fed, and swaddled comfortably while being monitored with continuous pulse oximetry before being placed in the MRI scanner. Standard, size appropriate, hearing protection will be used for all infants. Sequences will be performed to demonstrate brain anatomy and will include T1 3D 1 mm volumetric, T2 1 mm 3D volumetric scans, T2 TSE FLAIR, and T1SE MTC sequences. These sequences will also contribute to the analysis of any detected brain pathology. T2 SWI axial images will be performed to show calcification and blood products. Sequences for the detection of vascular injury and infarction will include diffusion sequences (b value = 2000), resting BOLD, and arterial spin labeling. ^1^H-MRS will provide chemical spectra of the brain to further analyze brain pathology and measurement of cerebral creatine content. For MR spectroscopy, the voxel will be placed over the white matter underlying the central sulcus within the centrum semiovale and spectra acquired with a long echo time (TE 135 ms) (Koob et al., 2016).

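### Aim 5 asks about feed source and creatine in the early postnatal period, but the only stated analysis linking feeds to infant creatine takes its outcome at term corrected age

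*Protocol article*

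**What the plan says.** All places are in the protocol article.

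- **Specific Aims, fifth aim:** "Determine whether dietary source of creatine (TPN, formula, or breast milk) is related to plasma or urine creatine concentrations in the early postnatal period". The exposure is the type of feed and the window is the early postnatal period.
- **Statistical Analysis, nutrition and infant creatine:** the sentence opens "The association between creatine, GAA, and amino acid content of nutrition sources (TNP, formula or breast milk" and ends "infant plasma and urine creatine at CPA will be assessed using a Spearman or Pearson correlation as appropriate". The exposure is the analyte content of the feed and the outcome is dated at CPA.
- **Statistical Analysis, early values:** "Preterm infant plasma and urine creatine and GAA concentrations and creatine:GAA ratio in the early postnatal period will be described and plotted". No link to feed is stated.
- **Statistical Analysis, weekly nutrition summary:** "Average creatine content from nutrition per week for each baby in the early postnatal period will be calculated". No stated association then uses this summary by name.
- **Statistical Analysis, comparison of feeds:** "Differences in creatine, GAA, and amino acid content of nutrition sources (TNP, formula or breast milk) will be determined using a one-way ANOVA", or a Kruskal-Wallis test. This compares feeds with each other, which is the fourth aim.
- **Nutrition sampling (under Figure 1):** a sample of the nutrition "being fed to each infant at the time of the blood and urine sampling will be collected".
- **Monitoring and Data Collection:** the feeding schedule over less than 24 hours before each sample is recorded, with weight and corrected age at that sample.

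**The concern.** An aim and its analysis should agree on exposure, outcome and time. Here they agree only on the outcome variable. The aim concerns the weeks in which the authors expect creatine to fall. The stated test concerns creatine at the due date, when most preterm infants are well past that period.

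If the plan is followed literally, the study will report creatine trajectories, and separately the composition of the feeds. It will give no estimate of how early circulating or excreted creatine differs between infants on TPN, formula and breast milk. An analysis devised later to fill the gap would be chosen after the data had been seen. That is avoidable, because the samples and feeding records it needs are already part of the study.

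**Working it through.** No figure in the plan bears on this point, so there is nothing to reproduce. The check sets the aim against the stated analyses and then works out how far apart the two time points are.

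**Step 1. Aim against stated test**

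| Element | Fifth aim | Only stated analysis linking feed to infant creatine |
|---|---|---|
| Exposure | Feed source: TPN, formula or breast milk | Creatine, GAA and amino acid content of the feed |
| Outcome | Plasma or urine creatine | Plasma and urine creatine |
| Time of outcome | Early postnatal period | CPA |
| Method | Not stated in the aim | Spearman or Pearson correlation |

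The time differs outright. The exposure differs on the plain wording of the aim. A Spearman or Pearson coefficient needs an ordered or numerical exposure, so it cannot test a source with three unordered categories.

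**Step 2. Does another stated analysis cover the aim?**

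- The early plasma and urine values are descriptive only.
- The weekly nutrition average is calculated but named in no association.
- The ANOVA or Kruskal-Wallis test has feed composition as its outcome, not infant creatine.
- The tests on maternal and infant characteristics are at CPA. Their dietary preferences item is the mother's (omnivorous, vegetarian or vegan, listed under maternal characteristics), not the infant's feed.

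None of these relates feed to early creatine.

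**Step 3. How far is CPA from birth?**

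The MRI/1H-MRS Data Acquisition section puts the scan at 40 weeks. Interval = 40+0 minus gestational age at birth, in weeks+days.

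| Group | Born at lower limit | Born at upper limit |
|---|---|---|
| 23+0 to 26+6 | 17+0 | 13+1 |
| 27+0 to 29+6 | 13+0 | 10+1 |
| 30+0 to 32+6 | 10+0 | 7+1 |
| 33+0 to 36+6 | 7+0 | 3+1 |

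The outcome is therefore taken about 3 to 17 weeks after birth. The article itself treats the two times as separate: the first aim is at CPA and the second in the early postnatal period.

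**Step 4. Rough size of the in-hospital data (assumed, not stated)**

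The documents give no discharge age. Assume 20 infants in each of the 4 preterm groups, gestational age uniform within each group, discharge at 35 to 38 weeks, plasma every 14 days and urine every 7 days. Samples per infant = whole number of intervals in the stay.

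| Assumed discharge (weeks) | Plasma samples | Urine samples |
|---|---|---|
| 35 | 170 | 375 |
| 36 | 205 | 445 |
| 37 | 240 | 520 |
| 38 | 280 | 600 |

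These are in-hospital outcome values for which no stated analysis examines a relation to feed. By contrast, the CPA correlation has at most one outcome value per infant for each of plasma and urine: 4 × 20 = 80 preterm infants, or 100 with the term group. The counts show how much material is available. They do not measure bias or lost precision, and the finding does not depend on them.

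**The case against.** The strongest reply is that the study is mainly descriptive, has no formal power calculation, and is reported in an article that condenses a fuller protocol. The dietary association is among the further objectives, and no participant, sample or primary comparison is harmed by the mismatch. The abstract also words the objective as dietary creatine intake against circulating and cerebral creatine, which gives some support to content or intake as exposure. All of this stands, and it lowers the severity. It does not remove the conflict, because the aim and the test are both stated in the article and name different times.

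Four stronger readings are tempting, and the documents do not support them.

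- **That TPN has ended by CPA, so about no infants are on it.** The scan description says "infants are brought to the MRI unit, fed, and swaddled comfortably", which makes this plausible. But no TPN duration is given, and the primary outcome list names TPN among nutrition sampled to discharge and at CPA.
- **That the planned test uses none of the in-hospital feed samples.** In the planned sentence, CPA dates the plasma and urine creatine. It does not clearly date the feed content, which could come from earlier samples. Only the in-hospital plasma and urine outcomes are clearly left out.
- **That the planned correlation is confounded because TPN belongs to the earliest ages.** The documents do not say when TPN is given. Confounding by age at sampling would affect an in-hospital analysis. At CPA all infants are at about the same corrected age.
- **That Aim 5 is the evidence needed to justify the later supplementation trial.** The Discussion rests that trial on the overall hypothesis of creatine depletion, not on differences between feed sources.

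**Conclusion.** The concern holds in a limited form. Aim 5 and the stated analysis disagree on the time of the outcome, by about 3 to 17 weeks from birth according to gestational group. They also disagree, less sharply, on the exposure. No analysis stated in the article answers Aim 5. A fuller protocol or analysis plan, not shown, might contain one, but the sentence in the article would still conflict with the aim.

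The conclusion rests only on the wording of the aims and the Statistical Analysis section and on CPA being 40 weeks. It needs no assumption about TPN duration, discharge age or which feed samples enter the CPA correlation. Severity is moderate: one specific aim is left without an analysis, no primary comparison is affected, and the wording can be corrected before analysis.

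**What to change.** Add to Statistical Analysis an analysis for the fifth aim, for example:

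*For each in-hospital sample, plasma and urine creatine will be related to the feed source at that sample and, as a second exposure, to the creatine content of that feed or the weekly creatine intake. A linear mixed model with a random intercept per infant will be used, adjusted for gestational age at birth and postnatal age at sampling.*

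The mixed model is one suitable choice. What is needed is a method that allows for repeated samples within infants and for feed source possibly varying with maturity. The analysis should also say how a sample is classified when an infant receives more than one source.

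Keep the CPA correlation as a secondary analysis, and state whether in-hospital or CPA feed samples supply its exposure. If the investigators actually intend only the CPA question, reword the fifth aim to say so.

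The cost is a few sentences and modest analyst time. The feed, blood and urine samples and the feeding record before each sample are already to be collected.
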